### Volunteer recruitment

Posters will be disseminated at the hospital to recruit participants. During their appointment at the Department of Gastroenterology in the First Affiliated Hospital of Nanchang University, volunteers who are interested in the study will undergo preliminary evaluations based on the inclusion and exclusion criteria. Additionally, the investigator will explain the purpose, process, and potential benefits and risks of this study, and the volunteers may choose to participate by signing the informed consent form. Next, the volunteers will undergo further screening to determine their eligibility. Eligible participants will receive the study intervention and follow-up. The following steps describe the formal intervention and follow-ups (Table 1).

**Table 1 Tab1:** Study and follow-up schedule

Item^1,10^		Screening	Baseline	Initial treatment		Maintenance treatment
		Visit 0	Visit 1	Visit 2	Visit 3	Visit 4
		Days −3 to 0	Day 0	Week 4	Week 8	Week 12
Basic demographics		X				
Vital signs, physical examination		X				
Allergies, medical history^2^, medication history^3^, surgical history^4^		X				
Smoking and drinking		X				
Gastroscopy		X^5^				X^6^
Abdominal ultrasound B^7^		X				
Serum human chorionic gonadotropin (hCG)		X				
ECG		X				X
Blood test, urine analysis, stool test (including occult blood)		X				X
Liver/kidney function^8^		X				X
Signed informed consent		X				
Inclusion/exclusion criteria verification			X			
Primary outcome measure	GM^11^ (metagenomics)	X		X	X	X
Secondary outcome measures	RDQ	X	X	X	X	X
	GSRS		X	X	X	X
	Faecal metabolomics^11^	X		X	X	X
	BMI ^9^		X	X	X	X
	LA grade	X				X
Safety measures	AEs			X	X	X
	SAEs			X	X	X
Compliance verification			X	X	X	
Concomitant medications		X	X	X	X	

^1^Visit window: 0 days for visit 1; ± 2 days for visits 2, 3, and 4

^2^Medical history: current and past illnesses, including peptic ulcer, gastritis, oesophagitis, cardiovascular and cerebrovascular diseases, cancer, and mental illness

^3^Medication history: PPI, histamine H2 antagonists, antibiotics, probiotics, prokinetics, gastric mucosal protectors, and other drugs for gastro-oesophageal reflux (including herbs)

^4^Surgical history: gastrointestinal surgeries, including gastro-oesophageal and duodenal surgeries

^5^Performance of gastroscopy in domestic tertiary or higher hospitals in the past 3 months

^6^Gastroscopy at visit 4, LA grades at visit 0 and visit 4 referring to patients with oesophagitis (LA-A, LA-B or LA-C)

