### Inclusion criteria

Consenting (Additional file 1: Appendix 3) patients with GERD or one of its signs after gastroscopy:In the past 3 months, gastroscopy performed at domestic tertiary hospitals has shown oesophagitis (LA-A, LA-B or LA-C);In the past 3 months, gastroscopy performed at domestic tertiary hospitals has not revealed oesophagitis, but there are symptoms such as heartburn, acid reflux, and poststernal burning pain; in addition, the RDQ score is ≥ 12 [18];
The subject’s age is 18–65 years (inclusive), male or female.

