### Secondary outcome

RDQ score: The RDQ (see Additional file 1: Appendix 5) includes 4 symptoms: heartburn, acid reflux, regurgitation, and noncardiac chest pain. Each symptom is rated on a 0–5 scale based on its frequency and severity in the last week. The total score is 40, and a higher score is associated with more severe symptoms. RDQ ≥ 12 indicates GERD [18, 21]. The RDQ will be used to evaluate reflux-related symptom scores on day 0 (week 0), day 28 (week 4), day 56 (week 8), and day 84 (week 12).GSRS score: The GSRS (see Additional file 1: Appendix 6) is a self-rating scale that includes 15 items in 5 subscales (abdominal pain, acid reflux, dyspepsia, constipation, and diarrhoea). Each item is rated on a Likert scale ranging from 0–3 (none, mild, moderate, mild) based on the severity of symptoms in the last week. The total score is 45, and a higher score is associated with more severe symptoms [22–24]. The GSRS will be used to evaluate gastrointestinal disease symptom scores on day 0 (week 0), day 28 (week 4), day 56 (week 8), and day 84 (week 12).Faecal metabolome (FM): Based on the faeces, FM from day 0 (week 0), day 28 (week 4), day 56 (week 8), and day 84 (week 12) will be evaluated. Stool samples will be extracted using the protein precipitation method, and the supernatant will be transferred to sample vials for mass spectrometry combined with liquid chromatography (LC–MS/MS) analysis. The original data will be subjected to peak alignment, retention time correction, and peak area extraction through the XCMS-Plus program. The structure of metabolites will be identified by accurate mass matching (< 5 ppm) and two-level spectrum matching, and the METLIN database will be retrieved. Missing values > 50% in the group will be deleted, and the data will be normalized. Multidimensional statistical analysis will then be carried out, including unsupervised principal component analysis (PCA), supervised partial least squares discriminant analysis (PLS-DA) and potential differential metabolite analysis. Metabonomic analysis could further identify the potential differential metabolites of probiotics in the treatment of GERD, and correlation analysis between the gut microbiota and metabolites could be performed.Change in the Los Angeles (LA) grade of oesophagitis: According to gastroscopy, the change in the LA grade of oesophagitis will be evaluated.Body mass index (BMI): BMI = weight (kg)/height (m)^2^. BMI will be measured in the morning using the same weight and height scales at each visit. Participants will be instructed to wear light clothing and take off their shoes (standing barefoot or wearing socks no thicker than 0.1 cm) during the weight and height measurements.AE rate: all the AEs collected as described below will be used to calculate the AE rate in each group.Treatment compliance will be monitored as described in the “Volunteer compliance monitoring” section. Although efforts have been made to promote treatment compliance, there may still be differences between the two groups due to AEs.

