### Statistical analysis

First, the intention-to-treat (ITT) analysis will be conducted between the two groups, including all the intended participants who do or do not complete the follow-up. Then, per-protocol (PP) analysis will be conducted in the four-subgroup datasets according to compliance (100%, ≥ 80%, 60–80%, and < 60%) to validate the robustness of the results. The datasets will be analysed as described below.

With a randomized block design, the nonparametric rank sum test and Friedman M test will be performed to analyse the difference in each outcome measure at each time point (see “Intervention Outcome Measures” for details) between the two groups, including the GM analysis, RDQ score, GSRS score, faecal metabolomics, and BMI. The significance level will be set to *P* = 0.05. Next, the paired Wilcoxon signed-rank test will be performed for pairwise intragroup comparisons to analyse the change trends for each outcome measure before, during, and after the probiotic intervention. The significance level will be set at *P* = 0.05/[k(k-1)/2], where k is the number of groups in the comparison. For analysis of the oesophagitis grade, the diagnosis of LA-B at baseline and LA-A at week 12 indicates that the patient's oesophagitis grade will have decreased by one level. If the grade is LA-C at baseline and LA-A at 12 weeks, the patient’s oesophagitis grade will have decreased by 2 levels. The number of oesophagitis grades reduced by 1 and 2 levels in each group will be calculated. Then, a chi-square (*χ*^2^) test will be performed. AE rates in the two groups will be compared by the *χ*^2^ test or Fisher’s exact probability test based on the occurrence frequency of AE, and the difference in treatment compliance will be also examined by the *χ*^2^ test.

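### The oesophagitis analysis counts only 1- and 2-level reductions and gives healing no level, so some healed patients drop out of the count under each plausible reading

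*Protocol article*

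**What the plan says.** The Secondary outcome section names the endpoint without restricting its direction: "the change in the LA grade of oesophagitis will be evaluated".

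The Statistical analysis section then fixes how it is scored, with two worked cases: "the diagnosis of LA-B at baseline and LA-A at week 12 indicates that the patient's oesophagitis grade will have decreased by one level", and "If the grade is LA-C at baseline and LA-A at 12 weeks, the patient’s oesophagitis grade will have decreased by 2 levels". The summary follows: "The number of oesophagitis grades reduced by 1 and 2 levels in each group will be calculated". A chi-square test is applied to the result. Baseline grade does not enter the test.

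Two other places matter:

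- Table 1, footnote 6, limits the grading to those who enter with oesophagitis (LA-A, LA-B or LA-C): "LA grades at visit 0 and visit 4 referring to patients with oesophagitis".
- The inclusion criteria also admit symptomatic patients in whom "gastroscopy performed at domestic tertiary hospitals has not revealed oesophagitis, but there are symptoms such as heartburn, acid reflux, and poststernal burning pain". The protocol therefore recognises absence of oesophagitis as an endoscopic finding.

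**The concern.** Both worked cases end at LA-A, and neither ends in healing. A normal oesophagus at week 12 is the best result this endpoint can show, yet the rule does not say how many levels it is worth. The count also stops at two levels, although a patient entering at LA-C could fall three if healed is a level of its own.

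A rule of this kind can record the best outcome as no reduction. The analyst has to choose a reading, possibly after the grades are known, and the choice can change the result. Deterioration has no place in the count either. Rabeprazole is given in weeks 1 to 8 and the second gastroscopy is at week 12, so change in either direction since week 8 is possible when the grade is read.

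**Working it through.** The plan states no figure to reproduce. The check applies the counting rule to each transition.

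**Inputs from the protocol article.** Entry grades are A, B and C (Inclusion criteria; Table 1, footnote 6). B to A is one level and C to A is two. Reductions of 1 and 2 levels are counted (Statistical analysis).

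**Three readings of no oesophagitis at week 12.**

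| Baseline to week 12 | Level below LA-A | Merged with LA-A | Not a grade |
|---|---|---|---|
| A to none | 1, counted | 0, not counted | no score |
| B to none | 2, counted | 1, counted | no score |
| C to none | 3, not counted | 2, counted | no score |
| B to A, C to B | 1, counted | 1, counted | 1, counted |
| C to A | 2, counted | 2, counted | 2, counted |
| Unchanged | not counted | not counted | not counted |
| Any worsening | no category | no category | no category |

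Each reading loses at least one group of healed patients: LA-C under the first, LA-A under the second, all under the third.

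**Size on an assumed mix.** The documents give no grade distribution. Assume 30 patients with oesophagitis in an arm (12 A, 12 B, 6 C), all healed at week 12.

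- Level below LA-A: missed = 6 LA-C; 6/30 = 20%.
- Merged with LA-A: missed = 12 LA-A; 12/30 = 40%.
- Not a grade: missed = 12 + 12 + 6; 30/30 = 100%.

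**Can the count fall when patients do better?** Assume a 50/30/20% A/B/C mix and these week-12 results:

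- A: none 80%, A 15%, B 5%.
- B: none 70%, A 15%, B 10%, C 5%.
- C: none 60%, A 15%, B 15%, C 10%.

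Then let LA-C patients do better: none 85%, and A, B and C 5% each.

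- Total healed: 0.50×0.80 + 0.30×0.70 + 0.20×0.60 = 73.0%, rising to 0.40 + 0.21 + 0.20×0.85 = 78.0%.
- Counted, level below LA-A: 0.50×0.80 + 0.30×0.85 + 0.20×0.30 = 71.5%, falling to 0.40 + 0.255 + 0.20×0.10 = 67.5%.
- Counted, not a grade: 0.30×0.15 + 0.20×0.30 = 10.5%, falling to 0.045 + 0.02 = 6.5%.
- Counted, merged with LA-A: 0.30×0.85 + 0.20×0.90 = 43.5%, rising to 0.255 + 0.20×0.95 = 44.5%.

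Under two of the three readings the measure moves the wrong way. Under the third it moves by 1 point where healing moves by 5.

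**Dependence on baseline mix.** Keep the first set of assumed rates and compare an A/B/C mix of 70/25/5% with one of 30/40/30%.

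- Any improvement: 0.70×0.80 + 0.25×0.85 + 0.05×0.90 = 81.75%, against 0.30×0.80 + 0.40×0.85 + 0.30×0.90 = 85.0%.
- Counted, level below LA-A: 0.56 + 0.2125 + 0.05×0.30 = 78.75%, against 0.24 + 0.34 + 0.30×0.30 = 67.0%.
- Counted, not a grade: 0.25×0.15 + 0.05×0.30 = 5.25%, against 0.40×0.15 + 0.30×0.30 = 15.0%.

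The grade-specific results are identical in both mixes, so these differences come from the mix alone. The mixes are deliberately far apart and do not predict the imbalance between arms.

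**The case against.** The best defence is that the two worked cases illustrate how levels are counted and are not a full algorithm. The endpoint is named in general terms, the article is a condensed account, and table layout, coding of non-improvers and small-cell handling are normally settled in an analysis plan that is not shown. A chi-square on reductions would ordinarily put everyone else in a not-reduced cell. Reading two levels as two or more would also rescue LA-C healing.

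Part of this stands. The absence of a table layout or a small-cell rule is not a fault in itself. The scoring is different: the article chose to state which reductions are counted, and that statement leaves out some healed patients. The words two or more are not there, and they would help only if healed were first made a level below LA-A.

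Four stronger inferences should be resisted:

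- **Healing from LA-C is never counted.** This does not follow, because it counts as two levels if healed is merged with LA-A.
- **The losses in LA-A and LA-C can be added, giving 18/30 or 60% in the assumed arm.** The 12 LA-A patients are lost only if healed is merged with LA-A. The 6 LA-C patients are lost only if it is the level below, or not a grade. If it is not a grade, all 30 are lost, so no single reading gives 18.
- **Ignoring baseline grade biases the comparison.** Allocation is random, so the grade mix is balanced in expectation and the unadjusted test remains valid.
- **The population for this analysis is undefined.** Footnote 6 of Table 1 already restricts grading to patients with oesophagitis.

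**Conclusion.** The point holds in a limited form. The stated rule gives no level to absence of oesophagitis at week 12 and counts only reductions of 1 and 2 levels, so each of the three plausible readings leaves some healed patients uncounted. In the assumed 12/12/6 arm with everyone healed, the share missed is 20%, 40% or 100%, depending on the reading. The protocol does not say which applies. These figures rest on an assumed mix and show scale only.

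Two lesser points go with it. Worsened patients are not distinguished from unchanged ones. The attainable reduction also depends on baseline grade, which the test ignores; no stratification of the randomization by LA grade is described, and only a subset of the 120 participants, of unstated size, will be graded. The consequence is lost precision and exposure to chance imbalance, not systematic bias.

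LA grade is a secondary outcome. The primary microbiome analysis and the sample size are unaffected. The plan should be corrected, but the trial's main conclusion does not turn on it.

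**What to change.** Replace the counting rule, before unblinding, with wording to this effect:

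- Analysis set: participants with LA-A, LA-B or LA-C oesophagitis at baseline, as footnote 6 of Table 1 already implies.
- Score: no oesophagitis = 0, LA-A = 1, LA-B = 2, LA-C = 3, LA-D = 4.
- Comparison: week-12 score between arms, by a van Elteren test stratified by baseline grade or a proportional-odds model adjusted for baseline grade. Name one of the two in advance.
- Description: a baseline-by-week-12 table of grades in each arm, so that healed, improved, unchanged and worsened patients are all visible.
- Complete healing (score 0) by arm, with Fisher's exact test if cells are small.

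The cost is a few sentences. The gastroscopies are already scheduled at screening and week 12 for these patients, so no data, visits or participants are added.

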## Discussion

Long-term use of PPIs in the treatment of patients with GERD affects their quality of life and causes discomfort and new problems such as dysbiosis of the gut microbiota. Probiotics may provide solutions and answers to patients’ questions regarding these issues. The amount of research in this area is limited, which is why this study was designed.

The probiotics used in the research were composed of *Lactobacillus casei Zhang*, *Bifidobacterium lactis* V9, and *Lactobacillus plantarum* P9. *Lactobacillus casei Zhang* can colonize the intestine, improve the structure of intestinal flora, affect the abundance of intestinal microbes, increase the metabolism of short-chain fatty acids, inhibit the formation of secondary bile acids, and have a positive and lasting impact on the intestinal microbiota of subjects [27]. Compared with *Lactobacillus acidophilus*, *Lactobacillus casei Zhang* has a stronger ability to improve the intestinal mucosal barrier and promote the expansion of beneficial metabolites, especially short-chain fatty acids and niacinamide [28]. *Bifidobacterium lactis* V9 has a stable colonization ability in the patient’s intestine. After 4 weeks of intervention, the structure and metabolism of the patient’s intestinal flora will change significantly, which can effectively regulate the patient’s gut microbial dysbiosis [29]. *Lactobacillus plantarum* P9 belongs to the genus *Lactobacillus*, which is one of the most widely studied probiotics. Many reports have demonstrated the improvement in gastrointestinal symptoms and the intestinal microbiota with *Lactobacillus* treatment.

Based on the effects of these three bacteria on the regulation of intestinal flora in the past, we suspect that the LiHuo probiotics used in this study can play a good regulatory role and provide a more comfortable and safe medication experience in patients who have used PPIs for a long time.

In addition, if PPI has detrimental effects on gastrointestinal tract homeostasis, concurrent probiotic administration with PPI may be more suitable rather than post PPI use. It may be interesting to confirm the effects of concurrent probiotic administration with PPI use on the GERD and even study the pros and cons between the two administrations of probiotics using along with PPI and post-PPI.

## Data Availability

Data sharing is not applicable to this trial, as no database was generated or analysed for the current study. When the study is completed, its results will be released to the public, volunteers, and the general medical community through the publication of journal articles, with all the related data made available.

## Abbreviations

AEs: Adverse events
ALT: Alanine aminotransferase
AST: Aspartate aminotransferase
BMI: Body mass index
ECG: Electrocardiogram
FM: Faecal metabolome
GM: Gut microbiome
GSRS: Gastrointestinal Symptom Rating Scale
GERD: Gastroesophageal reflux disease
PPIs: Proton pump inhibitors
RDQ: Reflux disease questionnaire
ULN: Upper limit of normal
Scr: Serum creatinine
SAEs: Severe adverse events
